#### Step 2: Determination of Diagnostic Errors in Trigger-Positive and Trigger-Negative Charts

This step aims to determine whether diagnostic errors are statistically more likely to appear in trigger-positive charts. We will investigate the presence of diagnostic error through manual review of a sample of trigger-positive and trigger-negative charts using the Revised Safer Dx instrument [35]. For each trigger, we will calculate the odds ratio of a diagnostic error for both trigger-positive and trigger-negative groups and perform appropriate hypothesis tests to decide if trigger-positive charts are more likely to result in a diagnostic error.

**Figure 2 figure2:**
[figure not shown]
Example of emergency department visit information flow. CT: computerized tomography; ECG: electrocardiogram; EMR: Electronic medical record; IV: intravenous; PT/INR: Prothrombin time and international normalized ratio.

**Figure 3 figure3:**
[figure not shown]
Emergency department context impacting the diagnostic process. ED: emergency department.

#### Step 4: Analysis of the Relationship Among Patient, Provider-Care Team, and System Factors and the Risk of Being Trigger-Positive

##### Overview

This step aims to analyze the trigger-labeled data sets obtained from the 2 institutions using different machine learning and data mining techniques. Data mining is a prevalent and effective technique for extracting nontrivial, implicit, previously unknown, and potentially useful knowledge from large data sources [37]. Discovering significant information related to disease diagnosis from medical databases is possible by applying techniques such as ARM [22], CHAID, and CART.

##### Association Rule Mining

ARM has been successfully applied in various medical contexts, from the discovery of adverse drug reactions to the identification of risk factors for heart disease [22]. ARM is one of the most significant unsupervised methods for pattern recognition [37], which explores frequently occurring patterns to find hidden associations between different factors. ARM will estimate the likelihood of trigger-positive risk through different factor combinations. Its predictive a priori model combines confidence and support into a single measure of predictive accuracy and discovers the best associations among the factors in large data sets [38]. Rules extracted by this method are usually represented in IF-THEN form, which makes it easier for medical experts to interpret and comprehend medical analysis [22].

##### Chi-square Automated Interaction Detection

CHAID is a decision tree algorithm that determines splitting based on statistical tests and has been used to model the relationship between the predictor variables and the outcome variable in many medical applications, such as identifying factors influencing inpatient mortality [17]. In our study, CHAID will help answer the question “Which combination of factors leads to higher trigger-positive risk and therefore a higher relative risk of diagnostic error?” CHAID splits the target into two or more categories using an exploratory analysis of the relationship between a dependent factor and several predictor factors [39]. To see if splitting the sample based on these predictors leads to statistically significant discrimination in the dependent measure (trigger labels), various independent factors will be evaluated using the chi-square test [40]. Despite regression, CHAID is capable of illustrating variable clusters through an iterative process. Adjusted *P* value measures are used to determine the best value of the partition or the best split, and splitting on a larger chi-square statistic indicates a more significant partition.

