#### Sampling for Control

The control includes visits that do not meet the criteria for any trigger. We will include all ED visits in the two health systems for the entire study period (July 1, 2017-December 31, 2019). For each trigger-positive case, we will match a single trigger-negative encounter based on the availability of cases through a hierarchical procedure, which matches the encounters based on age group, gender, provider, the reason for visit, and the arrival date and time. This one-to-one matching of trigger-positive and trigger-negative cases will also help to eliminate the imbalance classes. To accommodate the potential heterogeneity across sites, the measurements will be reported as site-specific quartiles [24]. For patients with multiple ED or hospital visits during the study period, each record will be considered separately.

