### Limitations and Strengths

We anticipate some difficulties and potential limitations to our forthcoming project. First, although we have based our analysis on the patients’ medical records, it is notable that this information is not always available at all sites. Our method potentially cannot be extended to EDs that do not have an integrated EHR system, as different EDs might use incompatible EHR systems to ours, which at least requires an adaptation phase. We intentionally chose the community and academic sites to learn more about the potential difference and have recruited clinicians at each site to determine important differences and help customize the trigger algorithms. We also believe that by incorporating commonly accepted and standard measurements in this study, any future translation to other health systems would be possible by a simple mapping to the database elements of the target EHR system.

Second, our approach to investigate the risk of diagnostic error for ED patients with care escalation or death within a certain period from ED discharge will not include many events, including those that occur within the same ED encounter, possible events in other hospitals, and flag records that meet trigger criteria but are not associated with diagnostic error. We will attempt to update our data exploration approach to reduce the rate of such false-positive triggers. Conversely, a strength of our study is that the simultaneous investigation of 2 separate health systems with both adult and pediatric EDs reduces the chance of biased conclusions. These limitations are balanced by several unique strengths of this study to help identify potentially associated contributory factors of diagnostic error in the ED.

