### Conclusions

The use of sophisticated data mining techniques to compare trigger-positive and trigger-negative records will enrich the list of risk factors that lead to diagnostic errors. To the best of our knowledge, this is the first application of exploratory decision tree techniques such as CART and CHAID to determine the relative importance of associated predictors of diagnostic error. Such techniques will help identify risk factors of diagnostic error using EHR data and inform the development of future dynamic ED-based decision support systems for monitoring and improving diagnostic safety.

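### Step 4 models trigger status, but the CHAID question, the Results and the Conclusions carry its findings over to diagnostic error, and a trigger-level association alone does not support that.

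*Protocol article*

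**What the plan says.** All references are to the protocol article.

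- **Outcome.** The Step 4 heading concerns the risk of being trigger-positive. CHAID looks for "statistically significant discrimination in the dependent measure (trigger labels"). For association rule mining (ARM), "ARM will estimate the likelihood of trigger-positive risk through different factor combinations", using a model that "combines confidence and support into a single measure of predictive accuracy". The CART subsection gives its nodes no risk meaning.
- **Inference.** CHAID is meant to answer "Which combination of factors leads to higher trigger-positive risk and therefore a higher relative risk of diagnostic error". The Results expect a better understanding of what contributes to diagnostic error. The Conclusions present the trees as a way "to determine the relative importance of associated predictors of diagnostic error".
- **Sampling.** Sampling for Control takes one trigger-negative encounter per trigger-positive one and "matches the encounters based on age group, gender, provider, the reason for visit, and the arrival date and time". It adds: "This one-to-one matching of trigger-positive and trigger-negative cases will also help to eliminate the imbalance classes". Step 1 describes the groups as matched on demographics and on comorbidity or severity.
- **Link to error.** Step 2 reviews a sample of charts from both groups with the Revised Safer Dx instrument and tests, trigger by trigger, whether error is more likely in trigger-positive charts. Limitations and Strengths concedes that the approach will "flag records that meet trigger criteria but are not associated with diagnostic error".

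**The concern.** The three initial triggers are return with admission, escalation to intensive care, and death. Each can follow from severe or progressing disease that was correctly diagnosed. A factor may therefore raise the chance of a trigger and leave the chance of an error unchanged. Moving from trigger to error for a given combination of factors requires that the predictive value of the trigger (PPV, the share of trigger-positive charts with an error) and the error rate among trigger-negative charts do not vary across combinations. Nothing in Step 2 tests this.

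At stake is the label put on the findings. Markers of deterioration or frailty could be published as predictors of diagnostic error and taken into the later aims under that name.

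A second, smaller matter is that 1:1 matching fixes the trigger-positive share of the mining set at one half. Rule confidence and node percentages from that set do not estimate how likely a trigger is in an emergency department.

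**Working it through.** The article states no PPV, trigger rate or node risk, so there is no figure to reproduce. The values below are assumptions, shown over ranges.

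**1. A factor that acts only on non-error triggers.** Set the trigger rate without the factor to 1, made up of PPV (error) and 1 − PPV (no error). The factor doubles the second part only.

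Trigger relative risk = PPV × 1 + (1 − PPV) × 2

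| PPV without factor | Trigger relative risk | PPV with factor |
|---|---|---|
| 10% | 1.9 | 0.10/1.9 = 5% |
| 20% | 1.8 | 0.20/1.8 = 11% |
| 50% | 1.5 | 0.50/1.5 = 33% |

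The relative risk of trigger-detected error is 1.0 in every row. That is an input, not a result. The table shows how strong a trigger signal such a factor would give.

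**2. A constant PPV.** Let t be the trigger rate in a stratum and e0 the error rate in trigger-negative charts.

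P(error) = t × PPV + (1 − t) × e0

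I take t = 4% against 2% (trigger relative risk 2.0), PPV 10% to 80%, and e0 1% to 9%. The upper end of e0 stays below the Introduction's figure of about one diagnosis in ten with some error.

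- PPV 20%, e0 5%: (0.008 + 0.048)/(0.004 + 0.049) = 0.056/0.053 = 1.06.
- Lowest (PPV 10%, e0 9%): 0.0904/0.0902 = 1.00.
- Highest (PPV 80%, e0 1%): 0.0416/0.0258 = 1.61.

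Here the direction carries over, because PPV exceeds e0, but the size does not.

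**3. A PPV that differs between strata.** With t = 4% against 2%, PPV 5% against 20%, and e0 1%:

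(0.0020 + 0.0096)/(0.0040 + 0.0098) = 0.0116/0.0138 = 0.84.

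The trigger risk doubles and the error risk falls.

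**4. What 1:1 sampling does.** With π the overall trigger rate and controls treated as unmatched:

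population odds = [c/(1 − c)] × [π/(1 − π)]

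- A rule with confidence c = 0.75 corresponds to a risk of 2.9% at π = 1% (odds 3 × 0.0101 = 0.0303) and 8.5% at π = 3% (odds 3 × 0.0309 = 0.0928).
- A true trigger relative risk of 2.0 (2% against 1%, 30% exposed) appears as node shares 0.608 and 0.434, ratio 1.40. The odds ratio, 2.02, is preserved.
- Lift for c = 0.75 is 0.75/0.50 = 1.5 in the sample but 0.0294/0.01 = 2.9 in the population at π = 1%, so lift does not escape the sampling.

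The plan matches individually on five variables, so these conversions are approximate. They show only that the two scales differ.

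**The case against.** Much can be said for the plan.

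- **A reader might infer that all of Step 4 treats rule confidence and tree nodes as error risk.** The article does not say so. ARM is described in terms of trigger-positive risk, CART nodes get no risk reading, and only the CHAID question makes the step, in relative terms. This stands, and limits the point to that question and to the Results and Conclusions.
- **A reader might infer that percentages from the 50:50 set will be reported as real-world risks.** No section says that. The Objective describes a search for factors most prevalent among trigger-positive cases. The ARM wording on estimating likelihood is the most that points the other way. This stands, so the sampling issue is a caution and not an error in the plan. Under unmatched sampling, odds ratios and the ordering of nodes survive.
- **Severity matching.** Step 1 says the groups are matched on comorbidity or severity, which would weaken the route through disease severity. The detailed list in Sampling for Control names neither. Matching on measured severity would reduce non-error triggers as an explanation, not remove it.
- **Chart review does more than select triggers.** It refines their criteria, and the limitations promise an attempt to reduce false positives. Fewer false positives help, but do not make the PPV constant across factors.
- **Findings do not pass straight into a tool.** The Objective leaves causal work to aim 2, and the Discussion places the prediction tool under aim 3. This stands, and lessens the harm.
- **The article is condensed.** Reuse of the Safer Dx results may be set out elsewhere. That would answer a complaint about omission. It does not answer an inference and conclusions that are stated in print.

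**Conclusion.** The point holds in a limited form. Step 4 can show which factors go with trigger status. It cannot by itself support the CHAID question's step to diagnostic error, or the matching language in the Results and Conclusions. Step 2 supplies at most an average link. The rule that opens Step 3 weakens even that: as worded, it keeps triggers for which the null hypothesis is not rejected. This looks like a reversal, and the point does not depend on it. The sample size section also names diagnostic error as the outcome, whereas Step 4 models the trigger label.

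On size, under assumed PPVs of 10% to 50%, a factor unrelated to error can show a trigger relative risk of 1.9 to 1.5. With a constant PPV, a doubled trigger risk implies an error relative risk between 1.00 and 1.61 over the ranges used, and with a differing PPV the direction can reverse. None of these inputs is in the article. The logical gap does not depend on them, but its actual size does.

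The documents do not support the stronger claims that the whole of Step 4 misreads its output as error risk, or that inflated absolute risks will be published.

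**What to change.** **(a) Check leading factors against reviewed error.** For the leading factors or rules from Step 4, analyse the Step 2 charts from both trigger-positive and trigger-negative groups, with Safer Dx error as outcome and weights for the sampling fractions. A comparison within trigger-positive charts alone is not enough. It tests only whether the PPV varies, so a factor that raises error and non-error triggers equally would show nothing, and one that merely lowers non-error triggers would pass. Call a factor a predictor of diagnostic error only if this analysis supports it. Otherwise report it as associated with trigger status. Reword the CHAID question, the Results and the Conclusions to match.

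**(b) Keep sample shares apart from real-world risk.** State that rule confidence and node shares from the 1:1 set are not population risks. Report odds ratios that respect the matching, or weight to the full cohort, which the Results say is already labelled, before quoting any risk. Do not rely on lift from the 50:50 set.

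**Cost.** No new data are needed beyond the planned chart review and trigger labels. The reviewed sample is smaller than the mining set, so only leading factors can be checked, with limited precision, and the claims become more modest.

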##### Classification and Regression Trees

CART analysis is another tree-based nonparametric data mining technique frequently used in medical diagnosis studies [23]. It has been widely used in the literature for both classification and interpretation tasks, such as identifying important predictive factors for persistent shoulder pain [41], ranking the risk factors for *Schistosoma mansoni* reinfection [42], and analyzing the risk factors of hypertension [43]. CART divides a large heterogeneous data set into smaller, more homogeneous nodes by employing recursive partitioning based on a target variable [23]. The significance of these decision rules is the definition of subgroups of patients and the most relevant interactions between them [44].

## Results

The entire study cohort is well specified and labeled by trigger scripts, and the data are undergoing cleaning and preparation for subsequent steps. Following the completion of this study, we expect to characterize common factors associated with both trigger-positive and trigger-negative charts by applying multiple machine learning-based factor analysis techniques. These algorithms explore different combinations of factors within all trigger-positive and trigger-negative cases to identify meaningful interactions of risk factors concerning each trigger. We have already provided a list of potentially important EHR-based factors for the triggers based on our literature review and previous experiences in practice. As listed in Textbox 2, some of these factors are common among all 3 triggers, and some are specific to a trigger based on the definition. We will also expand and explore a list of previously underinvestigated but recognized anecdotally as potential patient-, provider-care team–, and system-related factors that could be approximated by these variables (eg, estimating the effect of the cognitive burden by system and provider variables such as ED crowding).

List of potential electronic health record–based predictor variables extracted from previous studies.
**Factors Across All Triggers**
Demographics (eg, age and sex)Emergency department (ED) encounter (date and time [D/T])Chief complaintsClinical impression (tenth revision of the International Statistical Classification of Diseases and Related Health Problems [ICD10])Final ED diagnosis (ICD10)Hospital admission diagnosisED length of stayNumber of lab tests
**Trigger 1: Specific Factors**
Previous ED departure (D/T)Previous ED dispositionReturn ED arrival (D/T)Return ED dispositionReturn ED typeReturn ED chief complaintsReturn ED clinical impressionReturn ED diagnosis (ICD10)Return hospital diagnosis
**Trigger 2: Specific Factors**
ED discharge (D/T)Hospital dispositionNext unitIntensive care unit (ICU) unitTime-to-ICU (hours)
**Trigger 3: Specific Factors**
ED discharge (D/T)ED dispositionED departure (D/T)ED unitDischarge-to-death (hours)Hospital disposition

We have also updated the SQL queries of all 3 triggers to be compatible with the EHR databases at both sites. ED patients’ evaluations against each trigger are performed upon the execution of these queries on each EHR database. We reinforced multiple inclusion and exclusion criteria to the queries to ensure that test data or irrelevant information do not affect our selections. All queries share common information related to the initial encounter, followed by specific factors collected for each trigger separately. Figure 4 shows an example relational database schema on how different factors are being invoked and matched from multiple database tables to identify encounters with an escalation in the care condition, denoted by trigger 2.

The outcomes of this project include an improved understanding of the risk factors contributing to diagnostic error in the ED. The data could be used to inform EHR-based decision support systems for better prediction of the risk of diagnostic error in the ED. The first exploratory results of the project are expected to be submitted for publication by mid-2021.

**Figure 4 figure4:**
[figure not shown]
Emergency department patients’ evaluation against each trigger is done upon executing these queries on each electronic health record database. This figure is an example relational database schema on how relevant electronic health record–based predictive factors are being invoked from multiple database tables to build up a record of escalations in the care condition, denoted by trigger-2. Abbreviations in the figure represent arbitrary variable names as examples.

## Discussion

### Relevance

A strategy to address diagnostic error is the better use of health information technology and EHR data [45]. This project expands upon previous work on diagnostic errors by investigating risk factors through data mining techniques applied to EHR data. In particular, we aim to generate information relevant to the future design of a dynamic ED-based decision support system to enhance the quality of emergency care through large-scale analysis of EHR records. As a result of using unbiased machine learning techniques, we will find previously unexplored associations. These novel associations will help future investigations into causal risk factors for diagnostic errors.

Building on this in the future (Figure 1, aim 3), we will use machine learning approaches with patient and frontline provider factors to develop a real-time, dynamic, trigger-based EHR diagnostic error risk prediction tool. This will inform clinicians of potential risks based on the patients’ EHR records that could be preventable or addressed through appropriate intervention.

In contrast, interfacing with other systems such as health information exchanges may improve the completeness of clinical information on patients and may help improve the predictive value of triggers (such as when a return visit was in a nearby ED that participated in a health information exchange vs not). We will be open to exploring all kinds of such interactions, and if we see *signals* regarding medications or other systematic alerts, we will study them further by obtaining clinician’s insights for face validity and accuracy. Although we are not specifically focused on drug or medication-related events, if they contribute to the diagnostic process and breakdowns, they will be included as covariates.

### Limitations and Strengths

We anticipate some difficulties and potential limitations to our forthcoming project. First, although we have based our analysis on the patients’ medical records, it is notable that this information is not always available at all sites. Our method potentially cannot be extended to EDs that do not have an integrated EHR system, as different EDs might use incompatible EHR systems to ours, which at least requires an adaptation phase. We intentionally chose the community and academic sites to learn more about the potential difference and have recruited clinicians at each site to determine important differences and help customize the trigger algorithms. We also believe that by incorporating commonly accepted and standard measurements in this study, any future translation to other health systems would be possible by a simple mapping to the database elements of the target EHR system.

Second, our approach to investigate the risk of diagnostic error for ED patients with care escalation or death within a certain period from ED discharge will not include many events, including those that occur within the same ED encounter, possible events in other hospitals, and flag records that meet trigger criteria but are not associated with diagnostic error. We will attempt to update our data exploration approach to reduce the rate of such false-positive triggers. Conversely, a strength of our study is that the simultaneous investigation of 2 separate health systems with both adult and pediatric EDs reduces the chance of biased conclusions. These limitations are balanced by several unique strengths of this study to help identify potentially associated contributory factors of diagnostic error in the ED.

